## Abstract

**Background:**

Even before COVID-19, there has been an urgent need to expand access to and quality of mental health care. This paper introduces an 8-week treatment protocol to realize that vision—Technology Enabled Clinical Care (TECC). TECC offers innovation in clinical assessment, monitoring, and interventions for mental health. TECC uses the mindLAMP app to enable digital phenotyping, clinical communication, and smartphone-based exercises that will augment in-person or telehealth virtual visits. TECC exposes participants to an array of evidence-based treatments (cognitive behavioral therapy, dialectical behavior therapy, acceptance and commitment therapy) introduced through clinical sessions and then practiced through interactive activities provided through a smartphone app called mindLAMP.

**Objective:**

TECC will test the feasibility of providing technology-enabled mental health care within an outpatient clinic; explore the practicality for providing this care to individuals with limited English proficiency; and track anxiety, depression, and mood symptoms for participants to measure the effectiveness of the TECC design.

**Methods:**

The TECC study will assess the acceptability and efficacy of this care model in 50 participants as compared to an age- and gender-matched cohort of patients presenting with similar clinical severity of depression, anxiety, or psychotic symptoms. Participants will be recruited from clinics in the Metro Boston area. Aspects of TECC will be conducted in both Spanish and English to ensure wide access to care for multiple populations.

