## Methods

### Study

The study will take place at Beth Israel Deaconess Medical Center (BIDMC), a Harvard affiliated teaching hospital in Boston, Massachusetts. The care team will include a psychiatrist, social worker, and digital navigator. The psychiatrist and social worker will provide clinical treatment, education, and support for all participants. The digital navigator, as previously discussed, will be available for technology support and mindLAMP training to other care team members and research participants.

For this study, 50 participants will be enrolled and will not be financially compensated for their participation in TECC. Given the success of the pilot Digital Clinic program, including 50 participants is feasible and necessary to collect a diverse sample and see significant effects of different techniques on clinical assessments of depression and anxiety. This study will be open to any adult (18 years or older) who is interested in using smartphone technology to augment their mental health care. Participants are required to meet the criteria for either mild to moderate depression or anxiety as measured on the Patient Health Questionnaire-9 (PHQ-9) or Generalized Anxiety Disorder-7 (GAD-7) scale. Participants must have daily access to a smartphone, be willing to download the mindLAMP app, use their smartphone for mental health care (both in and outside of session time), and be open to learning about an array of clinical modalities (dialectical behavior therapy [DBT], cognitive behavioral therapy [CBT], short psychodynamic therapies). For participants who do not own a smartphone, the care team will help individuals sign up for a free phone through the US Federal Government’s Project Lifeline if they are eligible. Participants must also be affiliated with a BIDMC or Beth Israel Lahey Health provider and be available for eight clinical sessions (telehealth) over the course of 2-4 months. Until the Spanish language version of the mindLAMP app has been properly vetted, participants must be able to read, write, and communicate in English at an eighth grade level. Recruitment efforts for TECC include digital flyers and brief informational sessions for referring providers.

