### Analysis

Analysis will include calculation of the effect size of TECC to reduce symptoms related to stress, anxiety, and depression. Analysis will also focus on assessing association between baseline factors, race, language, and education, as well as dynamic factors like working alliance and technology engagement patterns with changes in symptoms and use and adherence to the TECC protocol. We will assess relationships between these factors and clinical changes using generalized linear models and multiple regression analyses. Tests for dropout effects will be performed to see if outcome and covariate measures are associated with differences in engagement. If there are significant dropout effects, a logistic dropout probability model will be fit using the significant dropout outcomes and covariates measured at the start of the stage, and inverse probability weighting will be used with these model probabilities to account for dropout in each of the models. The age-matched control group will be used to compare changes related to clinical scores and calculate effect sizes using means and SDs.

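### The between-group effect size may include self-selection: TECC entrants pass interest, access, willingness and availability criteria that the stated basis for choosing controls does not mention, and the contrast is unadjusted

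*Protocol article*

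**What the plan says.** The comparison group is described in two places. The Abstract (Methods) sets the 50 TECC participants against an "age- and gender-matched cohort of patients presenting with similar clinical severity" (of depressive, anxious or psychotic symptoms), in order to assess acceptability and efficacy. The Analysis section states: "The age-matched control group will be used to compare changes related to clinical scores and calculate effect sizes using means and SDs". Gender and severity are not mentioned there.

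Entry to TECC is set out under Methods, Study, and is much narrower. A participant must be an adult "interested in using smartphone technology to augment their mental health care" with mild to moderate depression or anxiety on the PHQ-9 or GAD-7. The section continues: "Participants must have daily access to a smartphone, be willing to download the mindLAMP app". It also requires willingness to use the phone for care in and between sessions, openness to several kinds of therapy and an affiliated network provider. Participants must "be available for eight clinical sessions (telehealth) over the course of 2-4 months". Until the Spanish app has been vetted, "participants must be able to read, write, and communicate in English at an eighth grade level". Recruitment is by digital flyers and by information sessions for referring providers.

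The Introduction describes a prospective cohort in which everyone enrolled receives TECC. Its main hypothesis is a response relative to the participant's own baseline.

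**The concern.** TECC participants have put themselves forward, have the technology and have time for a course of care. The article does not say whether the controls have any of these features. If such features go with better improvement under any care, part of a difference in mean change would reflect who entered TECC, not what TECC did. Similar age, gender and severity would not remove that part.

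This is the only between-group estimate of efficacy in the article. The Results section says the findings will be used to support or adapt the model of care, so a reader is likely to take the effect size as the benefit of TECC over other care.

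**Working it through.** **Step 1. Set the selection criteria side by side.**

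| Feature | TECC participants (Methods, Study) | Controls (Abstract; Analysis) |
|---|---|---|
| Age | 18 or older | matched in both places |
| Gender | no restriction | matched in the Abstract; not named in Analysis |
| Severity | mild to moderate on PHQ-9 or GAD-7 | similar in the Abstract; not named in Analysis |
| Interest in smartphone care | required | not stated |
| Daily smartphone access | required, with help to obtain a free phone if eligible | not stated |
| Willingness to use the app | required | not stated |
| Openness to several therapies | required | not stated |
| Network affiliation | required | not stated |
| Availability for eight sessions | required | not stated |
| English literacy | required until the Spanish app is vetted | not stated |

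Seven features decide entry to TECC and are not mentioned for controls. The two descriptions of the control group also disagree on gender and severity.

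**Step 2. Look for a method that would correct the imbalance.** The Analysis section has three candidates.

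- The generalized linear models and multiple regressions relate baseline and dynamic factors to symptom change and to adherence. They are not described as adjusting the TECC-control contrast.
- The inverse probability weights come from a dropout model. They do not address selection into TECC.
- The contrast itself is specified only as a comparison of changes, to "calculate effect sizes using means and SDs".

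None of the three removes an imbalance in the seven features.

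**Step 3. Ask which way the bias would run.** The article gives some reason to expect a link with outcome. The Discussion says that patients whose treatment suits their preferences are less likely to leave care. The Introduction links limited English proficiency to more severe long-term complications. Study Measures includes a scale of motivation to change. These make an upward bias plausible. They do not establish it.

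**Step 4. Size.** The article gives no control sample size, no SD and no data on these features among controls, so the bias cannot be calculated. The following shows its form only. Suppose a feature changes improvement by g SD. All TECC participants have it, because entry requires it, and a proportion q of controls have it. Then

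expected standardised difference = TECC effect + (1 − q) × g.

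With assumed q from 0.3 to 0.7 and g from 0.3 to 0.8:

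- smallest: (1 − 0.7) × 0.3 = 0.09 SD
- middle: (1 − 0.5) × 0.5 = 0.25 SD
- largest: (1 − 0.3) × 0.8 = 0.56 SD

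None of these inputs comes from the document. If q were 1, meaning that controls meet the same criterion, the added term would be zero. If g were negative, its sign would reverse.

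**The case against.** The strongest reply is that this is a condensed journal article. It gives the controls one clause in the Abstract and one sentence in the Analysis section, and a fuller protocol may add eligibility criteria. That stands as far as it goes. A reader might infer that controls are chosen on age, gender and severity and on nothing else, so that the cohort will contain people without a smartphone or with little English. The article does not say so. What remains is that it names its matching variables twice, inconsistently, and fixes an unadjusted contrast.

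Three further points also have force.

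- Interest and willingness cannot be matched, so no choice of controls removes the whole problem. The same limitation applies to any volunteer cohort with a non-randomised comparator, and the article never claims randomisation. This is why the wording of the conclusion matters as well as the choice of controls.
- Some of the criteria are softer than they look. The English requirement is temporary, and help with a free phone eases the access requirement. Being available for eight sessions is not the same as completing them. Further Study Details keeps dropouts in the analysis, so TECC is not a sample of completers.
- The main hypothesis is change from the participant's own baseline, and the stated objectives also include feasibility and practicality for people with limited English. The choice of controls does not touch these.

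**Conclusion.** The point holds for the TECC-control contrast in the Abstract and the Analysis section. As specified, that contrast compares people selected for interest, access, willingness and availability with people not stated to be so selected, and nothing in the plan adjusts for the difference. The effect size may therefore include self-selection.

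The size is unknown. The range of 0.09 to 0.56 SD above follows entirely from assumed inputs and shows only that the added term need not be small. A reader might go further and conclude that the comparison is biased in favour of TECC by a known amount, or that it carries a given false-positive rate. The documents support neither: the upward direction is plausible but not shown, and the Analysis section specifies no significance test for this contrast. Nor does the point undermine the within-group hypothesis in the Introduction, which makes no use of controls.

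The study can stand. Its between-group effect size should not be attributed to TECC as the plan is now written.

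**What to change.** 1. Reconcile the Abstract and the Analysis section so that both give the same matching variables.
2. Draw controls from patients who meet the observable entry criteria under Methods, Study: adult, same network affiliation, same care language during the English-only phase, PHQ-9 or GAD-7 in the same entry range, and smartphone access where it is recorded.
3. Adjust the between-group contrast for baseline score and for whatever demographics are available in both groups, in place of raw means and SDs alone.
4. State that interest and willingness cannot be matched, and report the result as a non-randomised association that may include self-selection.

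A filter on scheduled visits is better left out. It would alter the background care of the comparison group, and so change what TECC is being compared with.

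The cost is a somewhat smaller control pool, one adjusted model and a sentence or two of text. Nothing changes for TECC participants. How easily the criteria can be applied depends on where the controls come from, which the article does not say.

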**Results:**

The results of the TECC study will be used to support or adapt this model of care and create training resources to ensure its dissemination. The study results will be posted on ClinicalTrials.gov, with primary outcomes related to changes in mood, anxiety, and stress, and secondary outcomes related to engagement, alliance, and satisfaction.

**Conclusions:**

TECC combines new digital mental health technology with updated clinical protocols and workflows designed to ensure patients can benefit from innovation in digital mental health. Supporting multiple languages, TECC is designed to ensure digital health equity and highlights how mobile health can bridge, not expand, gaps in care for underserved populations.

**International Registered Report Identifier (IRRID):**

PRR1-10.2196/23771

## Introduction

Both the short- and long-term effects of the COVID-19 pandemic are already leading to a paradigm shift across the health care industry [1-3]. The pandemic has underscored systemic health disparities, clinician shortages, and financial strain that highlight the need for new innovation [4-6]. As the field looks toward technology to offer accessible and cost-effective solutions, now is the time to consider how digitally informed care can provide improved outcomes while reducing access inequities for marginalized communities [7-10].

It is clear that the rapid adoption of technology in health care, especially telehealth, has been catalyzed by COVID-19. The mental health field has also adopted telehealth quickly with one clinic converting to 100% digital visits within 72 hours [11]. Data suggests the mental health field is now the largest user of telehealth [8], with prior barriers toward adoption now largely overcome [12-14]. Although concerns around telehealth visits remain, especially around the impact on the therapeutic alliance, research suggests a positive response from both patients and clinicians with no clear harm to alliance documented [15].

Yet, the increased uptake of telehealth can only address access to a limited extent, and the unmet need for mental health care continues to expand during the pandemic. Marginalized communities remain at a higher risk for exposure and with lower access to care. The Centers for Disease Control and Prevention recently reported that, regardless of age, Latinos are four times more likely to contract COVID-19 than their non-Latino White counterparts [16], and rates of psychosocial distress have increased most in the Latino community compared to any other group [17]. Although telehealth can increase access to care for some, meeting the rapidly rising needs of underserved populations—linguistic barriers, financial strains, culturally competent providers—will require more than just virtual face-to-face health care visits.

To increase access to care, the Technology Enabled Clinical Care (TECC) protocol will offer all aspects of treatment in Spanish and English. Research has shown that individuals with limited English proficiency are less likely to seek out specialty treatment like mental health care and, when diagnosed, have more severe long-term mental health complications [18]. With an estimated 25.4 million Americans who speak English less than “very well” [19], it is imperative that the mental health care field take a more active stance in tackling this unmet need. Although the app will be available in both Spanish and English languages, the Spanish version of the app will first be tested and reviewed for linguistic and cultural appropriateness before being used in clinical practice. This will be done by asking bilingual individuals for app feedback, with a focus on language and images used within the app

TECC proposes a new approach to care that uses the most therapeutic elements of face-to-face mental health treatment with the accessibility and innovation of smartphone technology toward the goal of offering effective care that is accessible to all communities, including minority and underserved populations. Evidence suggests that short-term therapies—often 8-12 weeks in length—are as effective as longer-term treatments in terms of both immediate and longitudinal outcomes [20]. However, these short-term therapies often fail to realize their potential because of clinician nonadherence to protocol and patient nonadherence to out-of-session exercises and homework. This nonadherence is not intentional by either party but rather a natural and well-documented pattern. Using technology, it is possible to help ensure treatment remains focused, with clear acknowledgment that overregulation and correction by technology would itself cause harm. This issue has already been raised by many mental health clinicians who report that some technology-based therapy programs limit the therapeutic approach and flexibility needed to help patients [21]. Thus, there is a need for technology to help guide care and ensure it remains on track while offering both patients and clinicians the autonomy to respond to unique care needs and clinical leads. The TECC protocol assessed in this study will offer such a hybrid approach and is informed by the research literature, focus groups with patients and clinicians, and our team’s experiences offering this form of care.

We realized the potential for this unique treatment while developing and implementing a *Digital Clinic*, an outpatient short-term mental health program based in Boston, Massachusetts. As outlined in previous publications, the Digital Clinic is a method of health care treatment that allows providers the ability to use digital technology to augment all aspects of care [22]. Initial successes of the digital clinic model are reflected in case reports, successful clinical outcomes, and positive patient feedback. However, the digital clinic framework offers a model for more complex care where the clinician uses digital tools like apps with less direct guidance and structure. This model is appropriate for many patients and especially those with treatment-resistant depression but requires more active investment from both clinician and patient. With this in mind, it may be possible to achieve the same outcomes for many patients who can benefit from brief and more structured evidence-based therapies while providing guidance for clinicians who seek more direction in using technology in care. Thus, although the theoretical model, hands-on experience, and actual framing of the Digital Clinic are imbued in this new protocol, the clinical focus of structured, educational, and guided care is what separates TECC from the original Digital Clinic model.

Taken from the Digital Clinic framework, this protocol will use a digital navigator (or technology specialist), a new team member who is able to offer technical support and assistance in ensuring the patient is able to thrive with technology use, so clinical visits remain focused on care needs. The digital navigators for this study will include research assistants who have completed the 10-hour digital navigator training. Briefly, the training consists of 5 modules: core smartphone skills, basic technology troubleshooting, app evaluation, clinical terminology and data interpretation, and engagement techniques. These modules will teach digital navigators how to perform their main responsibilities of selecting smartphone apps for care, troubleshooting technology issues for both client and clinician, and ensuring app data is understood by all parties [23].

Furthermore, TECC seeks to balance clinician and participant autonomy while providing some structure and treatment pathways. Thus, the protocol was specifically designed to empower clinicians and participants to use smartphone technology by customizing data collection of both mental health surveys as well as sensor data (if agreed upon) toward ensuring each participant’s unique experience is captured. Although each session of the protocol offers exercises related to aspects of the app, which the participant should complete between sessions, these activities are defined broadly to meet diverse clinical needs and offer clinicians therapeutic flexibility. For example, using the app toward goal setting and tracking will be applicable in almost any scenario.

The eight-session structure included in TECC will provide the flexibility for clients to learn about different treatment modalities to gain broad exposure to evidence-based therapeutic skills and techniques while still ensuring treatment is focused on personal needs. The clinical skills incorporated in TECC were chosen from current research done on short-term mental health treatments, studies designed specifically to understand marginalized communities, and app-based mental health interventions. The protocol consists of three main stages:

Stage 1 “Creating the Clinical Foundation”: This stage will allow participants to learn and practice shared decision-making by cocreating treatment goals, identifying thought patterns, and identifying coping skills and defense mechanisms. The goal of this stage is for participants to develop a broad understanding of their thoughts and behaviors while beginning to identify strengths and need areas. Participants will also be introduced to clinical language and definitions for shared language to be established.Stage 2 “Building Clinical Skills”: Expanding from the skills learned in stage one, this stage will focus on teaching and practicing cognitive defusion and behavioral activation techniques. The goal for this stage is to expose participants to practical therapeutic skills that can be used across many situations and symptom management.Stage 3 “Solidifying Clinical Gains”: This stage introduces participants to mindfulness techniques, a diary card–like model, and patient activation and empowerment skills. The purpose of this stage is to ensure participants grasp all technical skills and clinical language reviewed throughout treatment to make informed autonomous decisions regarding treatment preferences.

This yearlong study will follow a prospective longitudinal cohort design where all participants will receive the same treatment and smartphone interventions. Based on our own Digital Clinic pilot data, we hypothesize participants will report a treatment response rate—defined as 50% symptom reduction—of improvements in anxiety and depression within the 8 weeks of treatment compared to their initial baseline. We also hypothesize that both rates of app engagement out of sessions, as well as therapeutic alliance measured during sessions, will be correlated with clinical improvements and suggest a mechanism of action for TECC. Furthermore the study will test the feasibility of providing technology-enabled mental health care within an outpatient clinical setting via virtual telehealth visits, explore the linguistic and cultural appropriateness of the smartphone app (mindLAMP) used in the study, and analyze the symptom changes of anxiety and depression for all study participants.

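### The efficacy hypothesis is a 50% response rate with no benchmark, while the primary outcomes and the planned control comparison are on score changes

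*Protocol article*

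**What the plan says.** The last paragraph of the Introduction carries the efficacy hypothesis: "we hypothesize participants will report a treatment response rate—defined as 50% symptom reduction—of improvements in anxiety and depression", to occur "within the 8 weeks of treatment compared to their initial baseline". The stated basis is the team's own pilot data. No expected rate and no rate to be exceeded is given. The other hypothesis in that paragraph concerns the correlation of engagement and alliance with improvement. The paragraph ends by saying the study will "analyze the symptom changes of anxiety and depression for all study participants".

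Elsewhere the outcome is a change in score:
- Abstract, Results: results will be posted "with primary outcomes related to changes in mood, anxiety, and stress".
- Analysis: "Analysis will include calculation of the effect size of TECC to reduce symptoms related to stress, anxiety, and depression". Regression models relate patient and engagement factors to clinical changes. The control group is used to compare changes in clinical scores, with effect sizes from means and SDs.

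Under Methods, Study: "For this study, 50 participants will be enrolled". That number is described as feasible and as needed to "see significant effects of different techniques on clinical assessments of depression and anxiety". On eligibility: "Participants are required to meet the criteria for either mild to moderate depression or anxiety", measured on the PHQ-9 or the GAD-7.

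**The concern.** A hypothesis should be answerable by the analysis that follows it. Here the hypothesis is a proportion of responders measured against baseline, and the analysis is a difference in mean change measured against a matched cohort. They differ both in scale and in comparator. With no benchmark rate, the hypothesis as worded can be neither confirmed nor refuted by any observed proportion. Two readers could take the same data and reach different conclusions on whether TECC worked, one from the response rate and one from the score comparison.

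A second issue arises only if someone resolves the ambiguity in favour of the response rate. A yes/no cut discards how much each person changed, which costs power in a study of 50. The cut also sits awkwardly with the entry criterion. A person may qualify on one scale and enter near zero on the other, where a 50% reduction is undefined (score 0) or is reached by a one-point drop (score 2 to 1). Yet the hypothesis covers both anxiety and depression.

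**Working it through.** **Step 1. The statements side by side**

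| Place | Scale | Compared with | Benchmark or test |
|---|---|---|---|
| Introduction, hypothesis | 50% response | own baseline | none |
| Introduction, end of same paragraph | symptom change | not stated | none |
| Abstract, Results | changes | not stated | none |
| Analysis | score change, means and SDs | control group | effect size |

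Only the hypothesis uses response, and nothing in the Analysis section takes it up.

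**Step 2. The sample size**

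The 50 cannot be reproduced, because no alpha, power, effect, SD or response rate is given. For scale only, at two-sided 0.05 and 80% power, n per group = 2(1.96 + 0.84)²/d². This gives 51 at d = 0.56 and 63 at d = 0.50.

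**Step 3. What the cut would cost if it were the test**

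Inputs from the document: 50 TECC participants. All other inputs are assumed: 50 in the matched cohort (its size is not stated), no dropout, two-sided alpha 0.05, baseline uniform 5 to 14, slope on baseline 0.5, comparator mean drop 2.5 points, residual SD 3.5 or 4.5. There were 4000 simulated trials per setting. The tests were a two-proportion z test of a reduction of 50% or more, a t test of change, and ANCOVA on the follow-up score.

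| Benefit, SD | Response | Change score | Baseline-adjusted | Change − response | Adjusted − response | Adjusted − change |
|---|---|---|---|---|---|---|
| 2 points, 3.5 | 61% | 72% | 80% | 11 | 19 | 8 |
| 2 points, 4.5 | 43% | 52% | 58% | 9 | 15 | 6 |
| 2.5 points, 3.5 | 81% | 89% | 93% | 8 | 12 | 4 |
| 2.5 points, 4.5 | 62% | 71% | 76% | 9 | 14 | 5 |

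Mean response rates at the 2-point benefit were 50% v 28% (SD 3.5) and 50% v 33% (SD 4.5). Over benefits of 1.5 to 3 points the three differences run about 4 to 12, 6 to 19 and 2 to 8 percentage points. The last is the gain from baseline adjustment alone and should not be counted as a cost of the cut.

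**Step 4. Sensitivity to the assumptions**

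Take a latent normal score cut at a threshold, with comparator response p0 and TECC response p1 = Φ(Φ⁻¹(p0) + d), 50 v 50. At p0 = 0.30:

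| d | Full score | Response | Loss (points) |
|---|---|---|---|
| 0.2 | 16.9% | 11.6% | 5.2 |
| 0.4 | 51.6% | 34.1% | 17.5 |
| 0.56 | 80.0% | 58.9% | 21.0 |
| 0.8 | 97.9% | 88.4% | 9.5 |
| 1.0 | 99.9% | 97.8% | 2.0 |

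With p0 from 0.10 to 0.50 and d from 0.2 to 1.0 the loss runs from about 2 to 36 points. The largest value is at p0 = 0.10, d = 0.56: 80.0% v 44.0%. With 40 per group the grid gives about 4 to 35. A further simulation, using a true 50%-of-own-baseline cut and a change SD of 4 to 5 points, gave about 8 to 27 at 50 per group. The direction did not reverse in any setting.

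**Step 5. Against the analysis actually described**

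The Analysis section works on uncut scores. If that comparison decides efficacy, the loss from the cut is 0.

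**The case against.** The strongest reply is that no responder test is planned. The primary outcomes are changes, the paragraph with the hypothesis also promises an analysis of symptom change, and the control comparison uses means and SDs. A reader might infer that the trial is throwing away power through its choice of endpoint. The document does not support that, because the score is not cut in any analysis it names. This part of the objection stands.

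It also stands that the hypothesis is a within-person statement, so a two-group power loss does not describe that sentence, and that every input except the 50 is assumed. The sample size rationale speaks of effects on assessments, not of response rates, so it does not tie the 50 to the response cut. Nor is it an error that a proportional criterion asks for different point drops at different entry scores: that is what such a criterion means.

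The objection does not remove the mismatch. An SAP may well specify the deciding test and the covariates, and their absence from an article is no fault. But the article itself states the hypothesis on one scale and describes the analysis on another, and the hypothesis has no benchmark against which it could be judged.

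**Conclusion.** The point holds as a mismatch between hypothesis and analysis. Efficacy is hypothesised as a 50% response rate against own baseline with no target or null rate. The primary outcomes and the control comparison are on score changes, and no analysis of the response rate is named.

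Lost power is a conditional consequence, not a property of the plan. If the response cut were used as the test at 50 v 50, the loss would be about 4 to 12 points against the change score and 6 to 19 against a baseline-adjusted score under the Step 3 inputs, and about 2 to 36 under other assumptions. It is zero if the described score comparison decides. The matched cohort's size, baseline distribution, SDs, comparator change and treatment benefit are all assumed.

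**What to change.** - Restate the efficacy hypothesis as the mean change in PHQ-9 and in GAD-7 versus the matched cohort.
- Name the score comparison in the Analysis section as the analysis that decides it, with adjustment for the baseline score in place of unadjusted means and SDs. Under the Step 3 assumptions the adjustment adds about 2 to 8 points of power over the plain change score.
- Report the 50% response rate as a descriptive secondary result with a confidence interval.

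The cost is wording and analysis only. It relies on the baseline and follow-up scores that the score comparison already needs. The small downside is that the headline becomes a mean difference in points rather than the more familiar response rate.
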